**Fig. 2 Fig2:**
[figure not shown]
SPIRIT diagram for the LACE trial. 6MWD six minute walking distance, ACE angiotensin converting enzyme, BIA bioimpedance analysis, DXA dual-energy X-ray absorptiometry, eGFR estimated glomerular filtration rate, EQ5D EuroQol 5D, FFQ Food Frequency Questionnaire, IMP investigational medicinal product, NEADL Nottingham Extended Activities of Daily Living, SPPB Short Physical Performance Battery

In addition, we are collecting data on adverse events, falls, hospitalisation, death and admission to institutional care. Consent is obtained for open-label follow up of participants for these outcomes collected from routine clinical data following the end of the 1-year study period. We are collecting data on usual physical activity and diet at baseline and 12 months using step counts measured by an OMRON pedometer and the Scottish Collaborative Group Food Frequency Questionnaire (FFQ) respectively; this will allow the interaction between treatment and protein intake (total, plant vs animal protein) to be ascertained.

### Statistical analysis

Analyses will be by group as randomised and will comply with the International Conference on Harmonisation (ICH) E9 ‘Statistical Principles for Clinical Trials’ [35]. Two-sided *p* < 0.05 will be taken as significant for all analyses. The primary analysis will be a repeated-measures, mixed-model between-group comparison of SPPB utilising all available data points during follow up. Initially, a test for treatment interaction between perindopril and leucine will be carried out and if not significant the main analysis will proceed using the full power of the factorial design; each intervention will be assessed separately as an independent hypothesis. Treatment effect estimates for all primary and secondary outcomes will be adjusted for baseline values, age, sex and minimisation variables.

Secondary outcomes will be analysed with similar methodology using repeated-measures, mixed-model, between-group comparisons. Unadjusted and adjusted analyses will be presented as already discussed. Sensitivity analyses will be performed to further test the effect of missing data both by multiple imputation and by assigning worst-possible result status to missing data points. A supplementary per-protocol analysis will be performed to examine adverse events in those taking at least 80% of their study medication.

No interim analyses are planned. Exploratory sub-group analyses will be performed, including examining differences in treatment effects by age (above and below median), SPPB (> 8 vs ≤ 8) and sex. A full Statistical Analysis Plan will be prepared and finalised prior to trial database lock, and will be made available as an additional upload on the *Trials* website once finalised.

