### Outcomes

The primary outcome for the trial is the Short Physical Performance Battery, measured at baseline, 3, 6, 9 and 12 months. The between-group difference in the SPPB across the whole follow up will be reported as the primary outcome, calculated using generalised estimating equations to incorporate repeated measures and missing data. The SPPB is a validated measure of lower limb function that reflects everyday activity. It is a powerful predictor of subsequent disability, institutionalisation and death in older people [32–34], and has more data validating its use in older people than any other measure of physical function. Secondary outcomes include between-group differences in muscle mass measured by dual X-ray absorptiometry, other measures of physical function, instrumental activities of daily living and quality of life. We also measure blood pressure, insulin resistance, hip bone mineral density and a panel of biomarkers to explore both mechanisms of disease and predictors of response to treatment. Key outcomes and times of collection are listed as part of the SPIRIT figure (Fig. 2).

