### Sample size calculation

We have taken a deliberately conservative approach and used the minimum clinically important difference (MCID) for the SPPB to ensure we have proof of efficacy. In order to detect a MCID in the SPPB of 0.5 points (anticipated SPPB of 8 in the placebo group and 8.5 in the intervention group, SD = 2.7 points [46]) with a power of 90% at α = 0.05, and assuming a correlation between time points of 0.7 as seen from previous work [26], we would require a total of 352 participants (88 for each of the four groups). Assuming 20% dropout at 12 months (a rate of attrition consistent with that seen in previous trials of ACEi in frail older people [26]), we therefore need to recruit 440 patients. This sample size will also have 90% power to detect a 5% difference in muscle mass at 12 months, assuming a baseline value of 19 kg (SD = 2.8) for total skeletal muscle mass [47].

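### The main factorial analysis goes ahead only if a low-powered interaction test is non-significant, although the sample size assumes that analysis without condition

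*Protocol article*

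**What the plan says.** The Statistical analysis section sets an order of testing: "a test for treatment interaction between perindopril and leucine will be carried out and if not significant the main analysis will proceed" and does so "using the full power of the factorial design; each intervention will be assessed separately as an independent hypothesis". The only significance level in that section is "Two-sided *p* < 0.05 will be taken as significant for all analyses", so the interaction test is read here as a 5% two-sided test. The article does not say what the primary analysis becomes if the interaction is significant. It announces a full SAP, to be finalised before database lock, which is not available here.

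The Sample size calculation section takes an "anticipated SPPB of 8 in the placebo group and 8.5 in the intervention group, SD = 2.7 points", "with a power of 90% at α = 0.05", "assuming a correlation between time points of 0.7 as seen from previous work", and concludes that "we would require a total of 352 participants (88 for each of the four groups". That number is raised to 440 for 20% dropout. The Outcomes section says that the SPPB is "measured at baseline, 3, 6, 9 and 12 months".

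**The concern.** The two sections do not fit together. The sample size treats the at-the-margins comparison as the analysis that will be done. The analysis section makes it the analysis that will be done only if a preliminary test on the same data permits.

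Three things follow. First, an interaction is estimated with twice the standard error of a main effect, so a non-significant result is poor evidence that the two effects are additive. Second, when there is no interaction, chance alone will close the gate in one trial in twenty, and the analysis on which the trial was sized is then no longer the main one. Third, the simple effects that might replace it (perindopril v placebo within one level of leucine, and the converse) are correlated with the interaction contrast that triggered the switch. Given a significant interaction, they are pre-selected to look large. At stake is whether each primary hypothesis is tested by a known procedure, with known error rate and power, that was fixed before the data were seen.

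**Working it through.** **Inputs (all from the article).** Difference 0.5 points; SD 2.7; correlation 0.7; one baseline and four follow-up measurements; two-sided alpha 0.05; power 90%; 88 per cell, hence 176 v 176 on each margin.

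**Step 1: reproduce 352.** For the mean of four follow-ups adjusted for one baseline, the variance factor is (1 + 3 × 0.7)/4 − 0.7² = 0.775 − 0.49 = 0.285. The effective SD is 2.7 × √0.285 = 1.441. The number per margin is 2 × (1.441 × (1.960 + 1.282)/0.5)² = 174.6, rounded up to 175. The total is 350, against 352 stated, and 352/0.8 = 440. The other variants tried do not reproduce it:

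| Analysis assumed | Total N |
|---|---|
| Four follow-ups, baseline-adjusted | 350 |
| Three follow-ups, baseline-adjusted | 380 |
| Change score, four follow-ups | 460 |
| One follow-up, baseline-adjusted | 626 |
| Mean of four follow-ups, no baseline | 950 |
| One visit, unadjusted | 1226 |

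A cell-wise comparison with 90% power would need 175 per cell, or 700 evaluable and 700/0.8 = 875 recruited. The stated number is therefore a margins number.

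**Step 2: standard errors and unconditional power at 0.5 points.**

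| Contrast | Standard error | Power |
|---|---|---|
| Main effect, 176 v 176 | 1.441 × √(2/176) = 0.154 | 90.2% |
| Simple effect, 88 v 88 | 1.441 × √(2/88) = 0.217 | 63.3% |
| Interaction, four cells of 88 | 1.441 × √(4/88) = 0.307 | 37.0% |

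**Step 3: type I error per factor, no true effects.** In a balanced 2 × 2 design the main-effect and interaction estimates are uncorrelated, so the margins test keeps 5.0% after a non-significant interaction. The overall rate is 0.95 × 0.05 + 0.05 × P(false positive given a significant interaction). The conditional probabilities come from simulation with 4 million draws.

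**Step 4: power at a true effect of 0.5 points, no interaction.** The overall figure is 0.95 × 0.902 + 0.05 × P(significant given a significant interaction).

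| Rule after a significant interaction (assumed) | False positive given significant interaction | Type I error overall | Power given significant interaction | Power overall |
|---|---|---|---|---|
| No test | 0% | 4.8% | 0% | 85.7% |
| One pre-named simple effect at 5% | 33.6% | 6.4% | 52% | 88.3% |
| Either simple effect, each at 5% | 65% | 8.0% | 99.7% | 90.7% |
| Margins analysis always (no gate) | n/a | 5.0% | n/a | 90.2% |

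For example, with one pre-named simple effect, 0.0475 + 0.05 × 0.336 = 0.064 and 0.857 + 0.05 × 0.52 = 0.883. Testing either simple effect with a Bonferroni correction gives about 6.9% type I error overall.

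The simulation assumes known variance and equal cells of 88.

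**The case against.** A reader might infer that the pre-test inflates type I error in itself. The article does not support that. The only test that it commits to is the margins test after a non-significant interaction. That test holds 5.0% conditionally, and the rule gives 4.8% overall if nothing else is tested. Inflation needs a fallback that the article does not state, and what to do after a significant interaction can properly be left to the SAP. This part of the objection stands.

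A reader might also put the worst figures together: 8.0% type I error and a fall in power to 63%. They belong to different rules. The 8.0% arises when either of two simple effects may count, and overall power is then 90.7%, so none is lost. The 63% is the unconditional power of a single simple effect; given a significant interaction it is 52%, and overall power under that rule is 88.3%. This also stands, and it limits the average harm.

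Finally, the gate has a purpose: under a strong or qualitative interaction, a margins effect reported alone can mislead. That is a good reason to show the interaction and the cell means. It is a weaker reason to let a test with 37% power for a 0.5-point interaction choose the primary analysis.

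The objection does not remove the rule itself. It is written in the article as a decision rule. A SAP that named a fallback would still leave the primary analysis chosen by the data; it could cure this only by overriding the rule.

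**Conclusion.** The point holds as a mismatch between the stated decision rule and the basis of the sample size. The plan sizes the trial on an unconditional 176 v 176 comparison (90.2% power) and then makes that comparison conditional on a weak test. With no true interaction, the powered analysis is displaced in 5% of trials. With a true interaction of 0.5 points, the gate misses it about 63% of the time.

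The average cost is modest. When there is no interaction, overall power is at worst 4.5 points below the unconditional analysis (90.2% to 85.7%). Type I error per factor lies between 4.8% and 8.0% according to an unstated fallback, so unqualified inflation should not be claimed. The heavier cost falls on the individual trial in which the gate closes: its primary analysis is undefined in the article, and any substitute would be taken up after the interaction result has closed the gate.

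These figures rest on the 5% level for the interaction test, balanced cells, and the baseline-adjusted four-visit model that reproduces 352. This should be fixed, but it does not invalidate the design.

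**What to change.** In the protocol and SAP, make the at-the-margins comparison of each intervention, in all participants as randomised, the primary analysis whatever the interaction p-value. Always report the perindopril-by-leucine interaction estimate with its 95% CI and the four cell means. Treat within-level simple effects as secondary: they qualify the interpretation and do not select the primary analysis.

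Each factor then has 5.0% type I error and 90.2% power under the plan's own assumptions, and 352 evaluable and 440 recruited are unchanged. The cost is wording, to be settled before database lock. The small downside is that, if a true interaction exists, the primary estimate is an average over the levels of the other treatment and must be read with the cell means.

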### Intervention

Participants are randomised to receive either perindopril 4 mg once daily or matching placebo, and to receive leucine 2.5 g three times per day or matching placebo. The perindopril/placebo is administered as oral capsules. Placebo and active capsules are identical in external appearance. Perindopril tablets are over-encapsulated with a hard gelatin capsule and backfilled with lactose. The placebo capsules are identical in appearance and packed with lactose. The starting dose of perindopril is 2 mg daily which is up-titrated to 4 mg after 2 weeks if tolerated and renal function, serum potassium levels and blood pressure remain within defined limits (potassium < 5.0 mmol/L, creatinine < 180 μmol/L and < 30 μmol/L rise from baseline, systolic blood pressure > 90 mmHg). Participants in the placebo group also undergo a ‘mock’ up-titration. If the 4 mg daily dose is not tolerated, participants are down-titrated to the original 2 mg daily. If 2 mg is also not tolerated, medication is withdrawn.

The leucine/placebo is administered as a powder. A 1.5-ml scoop is provided and participants are instructed to take three scoops (4.5 ml equivalent to 2.5 g of leucine/placebo) three times per day. The placebo is matching lactose powder. Participants are instructed that they should mix the powder with food or drink. Exploratory work with our local Older People’s Advisory Group indicated that mixing the leucine powder with food or drink was palatable, particularly if mixed with foods such as yoghurt or orange juice.

Randomisation is conducted via a centrally controlled, web-based Good Clinical Practice-compliant randomisation system, run by Tayside Clinical Trials Unit. Investigators at each site access the web-based system to randomise each participant at the end of the baseline visit. Randomisation is stratified by site. To ensure balanced assignment across critical variables, a minimisation algorithm is employed, using baseline age (> 80 vs ≤ 80 years), sex, SPPB score (> 8 vs ≤ 8), grip strength (> 25 vs ≤ 25 kg for males; > 15 vs ≤ 15 kg for females) and Charlson co-morbidity score (> 3 vs ≤ 3) to balance allocation across trial arms.

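### Site, the stratification factor of the randomisation, is missing from the stated adjustment set, so standard errors will be slightly too wide

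*Protocol article*

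**What the plan says.** All references are to the protocol article, Methods.

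- **Intervention.** "Randomisation is stratified by site". A minimisation algorithm is then described, using age, sex, SPPB score, grip strength and Charlson score. Site is not one of these variables.
- **Statistical analysis, first paragraph.** Estimates for all primary and secondary outcomes "will be adjusted for baseline values, age, sex and minimisation variables". The perindopril-by-leucine interaction is tested first. If it is not significant, "each intervention will be assessed separately as an independent hypothesis". A two-sided p below 0.05 "will be taken as significant for all analyses".
- **Statistical analysis, second paragraph (secondary outcomes).** "Unadjusted and adjusted analyses will be presented as already discussed". No unadjusted analysis is mentioned before this sentence.
- **Sample size calculation.** The design targets a 0.5-point difference with SD 2.7, "with a power of 90% at α = 0.05", "assuming a correlation between time points of 0.7 as seen from previous work". It needs 352 evaluable participants, 88 in each of four groups, and 440 recruited.

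**The concern.** The adjustment set is an explicit list. It even names age and sex on top of the minimisation variables that already contain them, yet it omits the one stratification factor. Stratifying removes between-site differences from the treatment comparison by design. A model without site still counts those differences as residual noise. The reported standard error then exceeds the true one, confidence intervals are too wide, and some of the precision gained by stratifying is lost.

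Two looser points of wording sit beside this. The list does not name the other randomised treatment. And the sentence on unadjusted and adjusted analyses points back to something that was never said, without defining the unadjusted version or ranking it. The ranking matters because the sample size depends on baseline adjustment.

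**Working it through.** **Inputs from the article.** Difference 0.5; SD 2.7; correlation between time points 0.7; alpha 0.05 two-sided; power 90%; one baseline and four follow-up visits (3, 6, 9 and 12 months); 352 evaluable, so 176 v 176 for each factorial main effect.

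**Step 1: reproduce the plan's figure.**
- One follow-up measure, no baseline term: n per margin = 2 × (1.960 + 1.2816)² × 2.7² / 0.5² = 612.8.
- Mean of four visits adjusted for baseline, equal correlations: variance factor = (1 + 3 × 0.7)/4 − 0.7² = 0.775 − 0.49 = 0.285.
- 612.8 × 0.285 = 174.6, so 175 per margin and 350 in total, against 352 stated.
- 352 / (1 − 0.20) = 440, as stated.
- Standard error at 176 v 176 = 2.7 × √0.285 × √(2/176) = 0.1537. Then 0.5/0.1537 = 3.254, and power = Φ(3.254 − 1.960) = 90.2%.

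Of the two-sided variants tried at 90% power, only this one gives the stated size. The others were a single follow-up (1,226), single-visit ANCOVA (626), single-visit change (736), unadjusted four-visit mean (950) and mean change (460).

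**Step 2: omit site.** Let s be the share of the model's residual variance that lies between sites. With allocation balanced within site, the true standard error is √(1 − s) times the reported one. Hence:
- inflation of the standard error = 1/√(1 − s);
- true alpha = 2 × [1 − Φ(1.960/√(1 − s))];
- power without site = Φ((3.254 − 1.960)/√(1 − s));
- power with site = Φ(3.254/√(1 − s) − 1.960).

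The values of s are assumed:

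| s | SE too wide by | True alpha | Power without site | Power with site |
|---|---|---|---|---|
| 1% | 0.5% | 4.9% | 90.3% | 90.5% |
| 5% | 2.6% | 4.4% | 90.8% | 91.6% |
| 10% | 5.4% | 3.9% | 91.4% | 92.9% |

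Before rounding, the loss runs from 0.2 to 1.6 points.

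**Step 3: a stable site effect.** If sites differ by a constant amount, baseline SPPB carries the same difference and adjustment removes most of it. With slope 0.7, a site share ICC of *total* variance leaves (1 − 0.7)² × ICC = 0.09 × ICC in the residual, against 0.285.
- ICC 2%: s = 0.0018/0.285 = 0.6%. SE 0.3% too wide, alpha 4.9%, power loss 0.1 points (90.4% v 90.3%).
- ICC 10%: s = 0.009/0.285 = 3.2%. SE 1.6% too wide, alpha 4.6%, power loss 0.5 points (91.1% v 90.6%).

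**Step 4: the accompanying wording.**
- *Other treatment left out.* If its true effect is e, the residual variance rises from 2.7² × 0.285 = 2.078 by e²/4. At e = 0.5 it becomes 2.140 (up 3%) and power falls from 90.2% to 89.4%. At e = 1.0 power is 86.7%.
- *Unadjusted, if that means no baseline SPPB.* The variance factor is 0.775, the standard error 0.2534, and power = Φ(0.5/0.2534 − 1.960) = 50.5%.

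**The case against.** The strongest reply is that this is small and belongs to the analysis plan. The error is conservative and cannot create a false positive. The documents give neither the number of sites nor any between-site variance, so every size above is assumed. Where the site effect is stable, baseline adjustment already absorbs most of it. All of that stands and keeps the point minor. It does not remove it, because the article does not leave the covariates to the analysis plan: it fixes a list for all primary and secondary outcomes, and that list lacks site.

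Three stronger readings are tempting, and the documents do not support them.

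- *That adjusted and unadjusted analyses compete as primary.* The word primary is indeed not attached to either. But the only rule given for the primary outcome is that its estimate is adjusted, the unadjusted sentence stands in the paragraph on secondary outcomes, and the sample size reproduces only with baseline adjustment. What remains is a back-reference to nothing and a missing label.
- *That the trial has about 50% power.* The 50.5% applies only if *unadjusted* drops baseline SPPB. The article does not define the word. If only the other covariates go, power stays near 90%.
- *That the other treatment is excluded from the model.* Assessing each intervention separately describes hypotheses, not model terms, and the preceding interaction test needs both factors. The article is silent on the main-effects model. In a balanced 2 × 2 design the omission causes no bias and, at the design effect, costs under one point of power.

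Nor do the documents say that SPPB assessors or equipment differ between sites. The one equipment statement, on bioimpedance, is that all sites use the same machine.

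**Conclusion.** The point holds, as a minor one. The stated adjustment set omits the stratification factor, and following it literally gives standard errors that are somewhat too wide. The consequence is lost precision, not bias or an inflated false-positive rate. It amounts to 0.2 to 1.6 points of power for an assumed site share of 1% to 10% of baseline-adjusted residual variance, and 0.1 to 0.5 points for a stable site effect of 2% to 10% of total variance. These figures also assume equal correlations of 0.7, 352 participants with complete data, and allocation well balanced within site. The silence on the second treatment and the stray cross-reference are matters of wording. Neither changes the planned analysis or its 90% power, provided that baseline SPPB is in the model.

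**What to change.** Add site, as a fixed effect or a random intercept, to the covariates stated for the primary and secondary models. A random intercept copes better with small sites.

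In the same edit:
- state that the main-effects model carries both treatment factors;
- replace the sentence on unadjusted and adjusted analyses with one that names the adjusted model as primary for both hypotheses, says which terms the unadjusted model drops, and calls it supportive.

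The cost is wording only. Site and both allocations are already recorded, and the article says that the full analysis plan will be finalised before database lock. Sample size and trial conduct do not change.

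### Giving every missing data point the worst-possible result makes one planned sensitivity analysis depend heavily on dropout imbalance and leaves it insensitive to a real effect

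*Protocol article*

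**What the plan says.** The Statistical analysis section of the protocol article makes the primary analysis a repeated-measures mixed model on all available SPPB follow-up data. It then adds two missing-data checks. One is multiple imputation; the other proceeds "by assigning worst-possible result status to missing data points". The second rule is not limited by arm, by reason for missingness or to deaths, and the text does not say which outcomes it covers. The same section sets a two-sided p < 0.05 that "will be taken as significant for all analyses".

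The Outcomes section has SPPB "measured at baseline, 3, 6, 9 and 12 months" and states: "The between-group difference in the SPPB across the whole follow up will be reported as the primary outcome". The Sample size calculation section gives the scale: "anticipated SPPB of 8 in the placebo group and 8.5 in the intervention group, SD = 2.7 points", an MCID of 0.5, a correlation of 0.7 between time points, and 20% dropout at 12 months.

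**The concern.** A missed visit, a withdrawal for an unrelated reason and a death would all be scored as the worst possible function. When the imputed value lies far from the expected mean, the estimate responds strongly to any difference in the proportion missing. A modest difference in dropout can then look like benefit or harm, and a real benefit can disappear.

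The other planned check may not fill the gap. The mixed model relies on missing at random. If the multiple imputation takes its usual form (the article does not say), it relies on the same assumption. The only departure from that assumption then tested is a single extreme value, which does not show where between the two the conclusion would change.

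If the rule also covers secondary outcomes, a further problem arises: a measure such as DXA muscle mass has no natural worst value.

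**Working it through.** **Inputs from the protocol article.** Means 8.0 and 8.5, SD 2.7, MCID 0.5, correlation 0.7, 90% power at two-sided 0.05, 352 evaluable, 20% dropout, 440 recruited (Sample size calculation and Statistical analysis sections); four post-baseline visits (Outcomes section). Each factor is compared at its margin, so 220 versus 220 recruited and 176 versus 176 evaluable.

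**Assumptions.** SPPB floor 0, with 1 as an alternative. Dropout is either complete from the first follow-up visit or accrues evenly over the four visits.

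**1. Reproduce the plan's own figure.** For a baseline-adjusted mean of four visits the effective SD is 2.7 × √((1 + 3 × 0.7)/4 − 0.7²) = 2.7 × √0.285 = 1.441. With a difference of 0.5 and 90% power this needs 175 per margin, 350 in total, against 352 stated. Power at 176 per margin is 90.2%, and 352/0.8 = 440. A baseline-adjusted whole-follow-up mean is therefore the right basis for the steps below.

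**2. Distance of the imputed value.** 8 − 0 = 8 points, and 8/0.5 = 16 MCIDs.

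**3. False difference with no treatment effect, 17% versus 23% dropout.** The shift is (difference in average proportion missing) × (mean − floor).
- All follow-up visits missed: 0.06 × 8 = 0.48. With a floor of 1: 0.06 × 7 = 0.42.
- Even accrual: one quarter, one half, three quarters and all of the final dropout is missing at the four visits, on average 0.625 of it. So 0.06 × 8 × 0.625 = 0.30. With a floor of 1: 0.06 × 7 × 0.625 = 0.26.

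A simulation (4,000 trials, 220 per margin, normal scores with equal correlation 0.7, baseline-adjusted four-visit mean) gave 0.48 and 0.30. These were nominally significant in 30% and 22% of trials.

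**4. How unusual is a 6-point imbalance?** If true dropout is 20% on both sides, the SE of the difference is √(2 × 0.2 × 0.8/220) = 0.038. An imbalance of 6 points or more in either direction then has a probability of about 12%. Six points is 0.06 × 220, about 13 participants.

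**5. Balanced 20% dropout.** Under the null the simulated rejection rate was 5.3% (all follow-up visits missed), so there is no false signal. With a true effect of 0.5:

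| Case | Expected effect | Simulated effect | Simulated SE | Simulated power |
|---|---|---|---|---|
| Complete data | 0.50 | 0.50 | 0.134 | 95% |
| Even accrual | 0.875 × 0.5 = 0.44 | 0.44 | 0.260 | 40% |
| All follow-up visits missed | 0.8 × 0.5 = 0.40 | 0.41 | 0.351 | 23% |

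The simple normal approximation gives 39% (0.438/0.260 = 1.68) and 21% (0.41/0.351 = 1.17) for the last two rows, hence a range of about 21–40%. Most of the loss comes from the spread that the zeros add, since the SE roughly doubles or more, and less from dilution.

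**6. True effect 0.5 with more dropout on active (23% versus 17%).**
- All follow-up visits missed: 0.77 × 8.5 − 0.83 × 8 = 6.545 − 6.640 = −0.10.
- Even accrual, average missing 14.375% versus 10.625%: 0.85625 × 8.5 − 0.89375 × 8 = 7.278 − 7.150 = 0.13.

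The simulation gave −0.10 and 0.13. In both cases the real effect is largely or wholly erased.

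**The case against.** The strongest reply is that this is a deliberately extreme scenario beside multiple imputation. It is not the primary analysis, and nothing lets it override the primary result. Loss of power and a pessimistic estimate are what such a scenario is expected to show. That stands, and it limits the severity of the point. It does not make a single extreme value informative about where the conclusion would change.

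A second reply is that large imbalance need not be expected. The Intervention section asks participants who stop both drugs to stay in follow-up, so stopping a drug for intolerance does not by itself make SPPB missing. This is fair: the article gives no reason to predict a 6-point imbalance. Chance alone, however, produces one about 12% of the time at 20% dropout.

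A third reply is that the floor value, the outcomes covered and the handling of deaths belong in the statistical analysis plan. For those details this is right, and they are not counted as omissions here. The rule itself is stated in the article.

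A reader might go further and infer that a 6-point imbalance alone manufactures a difference as large as the MCID. The article does not support that for its own primary outcome. The outcome spans the whole follow-up and the 20% dropout is stated at 12 months; with even accrual the figure is about 0.30. It comes close to the MCID, at 0.48, only at a single visit or if the imbalance is present from the first visit. Nor does the analysis measure dropout balance and nothing else: with balanced dropout it keeps its nominal error rate.

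**Conclusion.** The point holds as a worthwhile and inexpensive improvement to a secondary analysis. It is not a flaw in the primary analysis. As worded, the rule places missing SPPB values 16 MCIDs below the anticipated mean. A 17% versus 23% dropout split then becomes a false difference of about 0.30 to 0.48 points, and with balanced 20% dropout the power for a true 0.5-point effect falls from about 95% to about 21–40%.

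These figures rest on an SPPB floor of 0, which the article does not state; a floor of 1 gives 0.26 to 0.42 for the false difference. They also rest on the two dropout patterns assumed, and on simulated scores that are normal, unbounded and equally correlated. The 95% refers to complete data on 220 per margin; the plan's own target after dropout is 90%, so the fall is similar from either starting point.

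Two parts are conditional. The remark that no check would show the limits of missing at random depends on the multiple imputation being of the usual form. The remark about muscle mass depends on the rule extending to secondary outcomes. The article settles neither.

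**What to change.** In the Statistical analysis section, and in the statistical analysis plan before database lock, replace worst-value assignment with delta-adjusted multiple imputation for SPPB. Shift the imputed values downward by 0, 0.5, 1.0, 2.0 and more points, in each arm separately and in both, and report the shift at which the conclusion changes. The larger shifts keep a pessimistic scenario in the plan while showing what lies between it and missing at random.

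If a floor score is kept, confine it to SPPB after death, report it as a separate composite analysis, and do not apply it to unbounded outcomes such as muscle mass.

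The cost is a small extension of imputation already planned, plus a little more reporting. No extra data or participants are needed.
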